### Randomization and blinding

Participants fulfilling the abovementioned criteria will be randomly assigned in a 1:1 ratio to either cerebellar anodal tDCS or sham cerebellar tDCS using online software provided by Castor EDC. A protocol of permuted block randomization with randomly selected variable block sizes will be applied. Furthermore, in order to ensure an equal distribution of ataxia severity in both groups, the SARA score of a recent (pre-study) visit will be used as a stratification variable. The randomization procedure will be conducted by an independent researcher who subsequently picks one of the 100 five-digit codes from the neuroConn tDCS user manual that belongs to the specific tDCS mode (real or sham stimulation). This person is otherwise not involved in the study. The investigator applying tDCS, other investigators, and patients thus remain unaware of treatment allocation.

### Intervention and study procedures

At the beginning of the first visit, informed consent is obtained from each subject participating in the study after explanation of the aims, methods, benefits, and potential hazards of the study once more. Subjects can withdraw their consent at any time and for any reason without incurring any penalty or withholding of treatment on the part of the investigators.

#### Questionnaires

At various points in time during the study participants are requested to complete a number of questionnaires (Table 1) [5]. The EuroQol 5-Dimension 5-Level (EQ-5D-5L) is an ordinal quality of life scale that contains five questions addressing the domains of mobility, self-care, usual activities, pain / discomfort, and anxiety / depression, each with five answer options. In the final question, subjects rate their overall health on a visual scale from 0 (worst imaginable health status) to 100 (best imaginable health status). The Patient Health Questionnaire-9 (PHQ-9) is a 9-item instrument that is used in the screening, diagnosis, and follow-up of depression. Participants record how often they experienced each of these nine symptoms in the last two weeks, ranging from never (score 0) to nearly every day (score 3), thus resulting in a total score between 0 and 27 points. In the shortened 32-item version of the Profile of Mood States (POMS), 32 adjectives are presented and subjects determine to what extent (0 = not at all to 4 = very well) each of these is applicable to their current state. In this way, mean scores on five different mood domains can be evaluated, namely depression, anger, tensor, fatigue, and vigor. The institute for Medical Technology Assessment Medical Consumption Questionnaire (iMCQ) aims to compute the medical costs made by the participants in the last three months due to physical and mental complaints [35]. These costs are calculated by multiplying the price per unit of care and the volume of care for each item. As a possible confounder, the degree of physical exertion will be assessed using parts 1 and 4 of the long version of the International Physical Activity Questionnaire [36]. These address the amount of moderate and vigorous exercise and time spent walking in the last seven days at work (part 1), if any, and during recreation, sport, and leisure time (part 4), and will be expressed in Metabolic Equivalent of Task (MET)-minutes per week. The number of MET-minutes per week is computed by multiplying the energy requirements of the type of activity – 3.3 for walking, 4.0 for moderate exercise, and 8.0 for vigorous physical activity – with the amount of minutes per day and the number of days per week on which that activity is conducted. The total work MET-minutes and leisure-time MET-minutes per week will be summed. Finally, part II of the Friedreich Ataxia Rating Scale (FARS) will be used to evaluate activities of daily living. This scale includes nine items and ranges from 0 (no assistance needed) to 36 (fully dependent).

#### Cognitive and affective symptoms

In the last decades it has become increasingly clear that the cerebellum is not only involved in motor tasks, but also plays an important role in various cognitive functions, predominantly affect regulation, executive functioning, spatial cognition, and linguistic processing. Deficits in these domains in patients with focal cerebellar lesions or degenerative cerebellar disorders are collectively referred to as the cerebellar cognitive affective syndrome (CCAS) [7, 11, 12, 37, 38]. Recently, Hoche et al. selected the most sensitive tests to screen for cerebellar cognitive and affective dysfunction out of a comprehensive standardized neuropsychological examination and validated this 10-item bedside screening battery test, called the CCAS/Schmahmann syndrome scale, in a new cohort of patients with cerebellar diseases [39]. In addition to a total raw score (0 to 120 points), the authors provided cut-offs for each item, which determine whether a participant passed or failed this test. Possible, probable, and definite CCAS were subsequently defined as a failure at 1, 2, or ≥ 3 items, respectively. In the current study, we will apply this CCAS/Schmahmann syndrome scale and examine the influence of cerebellar tDCS on both the total raw score and the number of failed tests.

#### Neurological examination and quantitative motor tests

A standardized neurological examination will be conducted and includes an assessment of ataxia severity (SARA), which will be videotaped and rated by two highly experienced investigators who are blind to randomization status and point in time. The Inventory of Non-Ataxia Signs (INAS), a clinical assessment instrument containing 30 items, will be used to determine the amount of extracerebellar involvement and results in an INAS count ranging from 0 (no non-ataxia signs) to 16 (very severe extracerebellar signs) [40]. More quantitative motor tests include two trials of the 8MWT, two trials of the 9HPT for each hand, and two trials of the PATA repetition rate task, which provide measures of gait speed, upper limb dexterity, and articulation speed, respectively [41]. In the former, the time will be recorded that it takes for a participant to walk a distance of 8 m as quickly as possible but safely. In the 9HPT, subjects are asked to fill the nine holes of the peg hole board with pegs one at a time as quickly as possible and then, without pausing, to remove them again one at a time. Lastly, in the PATA repetition rate task subjects repeat the “PATA” phrase as quickly as possible for ten seconds. The number of PATA repeats will then be counted.

#### Transcranial magnetic stimulation

The inhibitory influence of the cerebellum on the contralateral primary motor cortex (M1), a physiological phenomenon called cerebellar brain inhibition (CBI), can be evaluated using a dual-coil TMS paradigm. CBI can be demonstrated by a reduction of the motor evoked potential (MEP) amplitude when a test stimulus over M1 is preceded by a conditioning stimulus administered over the contralateral cerebellar hemisphere with an interval of 5 to 7 ms [42]. In patients with cerebellar ataxia due to lesions in the cerebellar efferent pathway, CBI is either significantly reduced or absent [43–45].

The CBI paradigm will be applied at T0 and T1. Conditioning stimuli will be delivered to the posterior and superior lobules of the right cerebellar hemisphere at a point 1 cm below and 3 cm lateral to the inion on the line joining the external auditory meatus. Although both double-cone coils and figure-of-eight coils have been previously utilized for this purpose, a recent systematic review concluded that the majority of CBI studies argued for the former [46]. Because the double-cone coil generates a larger electromagnetic field as compared to the conventional figure-of-eight coils and is therefore able to reach deeper target tissues, we also decided to use this coil (Magstim 110 mm) in the administration of cerebellar conditioning stimuli. Indeed, Hardwick and colleagues could not elicit CBI using the figure-of-eight coil in healthy young individuals, even at intensities of 65–80% maximum stimulator output, whereas CBI was readily present at all intensities when using the double-cone coil [47]. The coil will be oriented such that an upward brain current is achieved. A Magstim 70 mm figure-of-eight coil will be used to excite the hand representation of the left primary motor cortex with the handle pointed 45° posterolaterally to the midsagittal plane. MEPs are registered from the first dorsal interosseus muscle of the right hand through Kendall H69P surface electrodes in a belly-tendon montage.

After localizing and marking the motor hotspot on the tight-fitting cap worn by the participant (in order to guarantee a constant optimal coil position throughout the experiment), the resting motor threshold (rMT) will be assessed. The latter is defined as the lowest stimulator output to elicit MEPs (≥ 50 μV or visible by contraction) in five out of ten trials during muscle relaxation. The intensity of the cerebellar conditioning stimuli is set at 90% rMT of the contralateral M1 [29, 31, 48–51], while the intensity of motor cortex test pulses will be adjusted to produce MEPs with peak-to-peak amplitudes of 0.5–1.0 mV. Although it is true that the studies that delivered cerebellar conditioning stimuli at an intensity of 90% rMT obtained from M1 made use of a figure-of-eight coil, it can be assumed that a similar and more reliable effect can be accomplished by a double-cone coil.

Twenty trials will be conducted for each interstimulus interval (3 ms, 5 ms, 10 ms, and test pulse only) and presented in a pseudorandomized sequence. The ratio between the mean MEP amplitude after application of the dual-coil paradigm and the test stimulus will be calculated for each interstimulus interval.

#### Delay eyeblink classical conditioning

Delay eyeblink classical conditioning refers to a motor learning paradigm, which is dependent on the structural and functional integrity of cerebellar circuits [52]. In healthy individuals repeated time-locked coupling of an auditory tone (conditioned stimulus, CS) and a supraorbital nerve stimulus or corneal air puff (unconditioned stimulus, US) ultimately leads to the presence of a conditioned eyeblink (conditioned response, CR) prior to the US. Patients with degenerative cerebellar disorders and focal cerebellar lesions have been reported to show significantly diminished acquisition of CRs and no retention when multiple eyeblink conditioning sessions are applied [53–55]. Notably, the acquisition process already seems to be disturbed during the preclinical stage of SCA3 [33, 56].

In this study, we aim to investigate whether diminished acquisition of CRs in SCA3 patients is a static trait, which we postulated before, or whether this process could be enhanced by a two-week treatment with cerebellar anodal tDCS. To this end, we will apply a validated protocol previously described by Teo and colleagues and also used in our own study on preclinical SCA3 mutation carriers [56, 57]. Patients will be comfortably seated in a chair, having their back turned to the computer screen so they cannot see when the CS and US are presented. The US consists of an electrical stimulus (250 V, 200 μs duration) generated by a Digitimer DS7A that stimulates the right supraorbital nerve through a pair of Kendall H69P electrodes. The cathode is placed in the supraorbicular fossa, the anode 2 cm above the cathode. The stimulus level will be determined individually by multiplying the sensory threshold intensity by a factor 7 to 10. Two pairs of Kendall H69P electrodes will be used to record the electromyographic activity from both orbicularis oculi muscles. The active and reference electrodes will be placed just caudal to the lower eyelids and 2–3 cm from the lateral canthi, respectively. The CS consists of a loud auditory tone, presented via binaural headphones, and precedes the US by 400 ms, eventually co-terminating with it.

The conditioning protocol comprises six blocks of eleven trials: trials 1–9 are CS-US-paired, trial 10 is CS-only, and trial 11 is US-only. Trial 10 is inserted to ensure that acquisition of CRs occurs independent of the US. Extinction will be tested for by including a seventh block of eleven CS-only trials. Using this protocol, the percentage and timing of acquired conditioned responses will be assessed as well as the occurrence of extinction.

#### Static posturography

Static posturography will be performed to provide a quantitative, kinetic measure of standing balance performance compared to the more descriptive SARA stance item. To this end, subjects are asked to stand barefoot on a 60 × 40 cm force plate (Motekforce Link), which measures the excursion of the center of pressure (CoP) in the anteroposterior and mediolateral directions at a sampling rate of 1000 Hz. For each participant the “optimal” intermalleolar distance will be determined, defined as the smallest distance between the left and right medial malleolus in steps of 5 cm at which a subject stands comfortably without a tendency to fall. This value will be used throughout the study. Fixed lines are applied to the force plate to facilitate these measurements. Participants are instructed to look straight ahead at a fixed target at the wall with their arms relaxed along their body and stand as quietly as possible during three trials of 30 s each with pauses in between. The investigator will stand next to the subject for safety reasons.

#### Cerebellar transcranial direct current stimulation

Cerebellar tDCS will be delivered by two 7 × 5 cm rubber electrodes, which are connected to a neuroConn constant current stimulator. Similar to the set-up applied by Benussi and colleagues [29], the anode – encased in a dampened sponge envelope – will be placed in the midline 2 cm below the inion in order to reach both cerebellar hemispheres, while the cathode is attached to the skin overlying the right deltoid muscle. The anode and cathode are coated with electroconductive gel and paste, respectively, to maintain impedance levels below 5 kΩ throughout the stimulation. Elastic gauzes and tape are used to ensure fixation of the electrodes.

Following a ramp-up time of 30 s, as recommended previously to ensure proper blinding and reduce side effects [58], in which the current intensity is gradually increased from 0 to 2 mA, a maintenance current of 2 mA will be delivered for 20 min in case of real cerebellar stimulation (0.057 mA/cm^2^). Hereafter, the current is gradually decreased to 0 mA again during a fade-out period of 30 s. In sham sessions, the duration of real stimulation by convention is 40 s (i.e., 1200 / 30), directly preceded and followed by 30 s of ramp-up and ramp-down. The remainder of the time (i.e., 1160 s) consists of continuous impedance control without any stimulation. This is accomplished by the occurrence of a small current pulse every 550 ms (110 μA over 15 ms, peak current duration 3 ms) that enables reliable detection of bad electrode contact or disconnection. Both conditions will thus be indistinguishable with respect to electrode set-up, session duration, and physical sensations. After two weeks of stimulation, patients are asked to which group they think they were allocated.

Participants may experience mild itching, prickling, or burning sensations underneath the electrodes that disappear after a while. Considering the extensive exclusion criteria, the screening procedure, and constant monitoring of the subjects, we do not expect serious adverse events. The risks of tDCS are considered negligible. No serious adverse events have been reported [23, 59] and the similar stimulation protocol used by the Italian group yielded no side effects [29]. In any case, the investigator will make sure that the stimulation is fully tolerable at the beginning as well as throughout the experiment. Measurements will be terminated whenever the participant does not tolerate the measurement or whenever the investigator believes it is not safe to proceed.

### Outcome measures

The various outcome measures are listed in Table 2.

### Statistical analysis

Statistical analyses will be conducted using SPSS and, in general, the significance level is set at *p* < 0.05. Where appropriate, we will use either chi-square tests, t-tests, or two-way ANOVAs with TIME as within-subject factor (number of levels depending on the specific outcome measure, ranging from two to five) and TREATMENT as between-subject factor (anodal tDCS versus sham tDCS). Subsequently, Bonferroni-corrected post-hoc testing is performed to explore significant main effects. Possible correlations with functional scores will be addressed using Spearman’s rank-order correlations.

This study is exploratory in nature. In the previously conducted Benussi et al. trial, the authors included 20 patients with a variety of ataxias and were able to demonstrate significant differences between the stimulation and sham groups in SARA, ICARS, 8MWT, and 9HPT [29]. In the current study, the same sample size of 20 SCA3 patients is chosen (*n* = 10 real stimulation, n = 10 sham stimulation). Based on the data presented in the aforementioned study, a calculation (G*Power 3) revealed a power of 83% to detect significant differences when using SARA as the primary outcome measure (effect size 0.46, α = 0.05, sample size 20).

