**Methods/design:**

An investigator-initiated, double-blind, randomized, sham-controlled, single-center trial will be conducted. Twenty mildly to moderately affected SCA3 patients (Scale for the Assessment and Rating of Ataxia score between 3 and 20) will be included and randomly assigned in a 1:1 ratio to either cerebellar anodal tDCS or sham cerebellar tDCS. Patients, investigators, and outcome assessors are unaware of treatment allocation. Cerebellar tDCS (20 min, 2 mA, ramp-up and down periods of 30 s each) will be delivered over ten sessions, distributed in two groups of five consecutive days with a two-day break in between. Outcomes are assessed after a single session of tDCS, after the tenth stimulation (T1), and after three, six, and twelve months. The primary outcome measure is the absolute change of the SARA score between baseline and T1. In addition, effects on a variety of other motor and neuropsychological functions in which the cerebellum is known to be involved will be evaluated using quantitative motor tests, static posturography, neurophysiological measurements, cognitive assessment, and questionnaires.

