### Patient population and eligibility criteria

In order to be eligible to participate in this study, a subject must meet all of the following inclusion criteria:Age 16 years or older.Proven mutation in the *ATXN3* gene.SARA score between 3 and 20 at a recent (pre-study) visit. The SARA score reflects ataxia severity and ranges from 0 (no ataxia) to 40 (very severe ataxia) [32]. We previously distinguished between the asymptomatic, preclinical, and ataxic stage of SCAs and proposed definitions for each of these [33]. As about 20% of healthy controls in the SARA validation study were found to have positive ratings in at least one item, we defined clinically manifest ataxia as SARA ≥ 3 and this value will therefore be used as lower cut-off in the current trial. Further analysis of the results of the Benussi et al. study suggested that improvements following cerebellar anodal tDCS were greater in clinically less affected patients [29]. This indicates that a window of opportunity exists, probably related to the fact that in later stages of the disease there is severe neuronal loss and thus an absence of target cells to channel the tDCS effects. In this regard, Rubinsztein and Orr even speculate about a point of no return when a certain threshold of neurodegeneration has been exceeded and beyond which introduction of disease-modifying treatments may be futile [34]. In the current study, we therefore deliberately do not include SCA3 patients who are already wheelchair-bound but rather aim for mildly to moderately affected individuals, using an arbitrary SARA upper cut-off value of 20.

Exclusion criteria are:Epilepsy.History of brain surgery.Metallic implants in or near the skull.Presence of a pacemaker.Significant comorbidities that interfere with activities of daily life.(Suspicion of) pregnancy.Severe skin disease affecting the location where the tDCS electrodes will be placed.

Similar to the riluzole trial [16], we deliberately chose not to exclude patients who are receiving physical therapy or who are using centrally acting neurological medication, as we here plan to study the symptomatic effect of cerebellar tDCS added to any ongoing treatment reflecting current daily practice.

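### The primary SARA comparison does not adjust for baseline SARA although randomisation is stratified on it, and the ANOVA follow-up names main effects rather than the TIME × TREATMENT interaction

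*Protocol article*

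**What the plan says.** The abstract fixes the primary outcome: "The primary outcome measure is the absolute change of the SARA score between baseline and T1". Table 2 agrees. It lists the SARA change at T1 alone as primary and puts SARA at the other time points in a separate secondary row.

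Under Randomization and blinding, "the SARA score of a recent (pre-study) visit will be used as a stratification variable". Eligibility requires a "SARA score between 3 and 20 at a recent (pre-study) visit", and Table 1 schedules SARA at T0 for every patient.

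The Statistical analysis section gives one list for all outcomes: "Where appropriate, we will use either chi-square tests, t-tests, or two-way ANOVAs with TIME as within-subject factor", with TREATMENT as the between-subject factor and the TIME factor described as "number of levels depending on the specific outcome measure, ranging from two to five". Then "Bonferroni-corrected post-hoc testing is performed to explore significant main effects". No test is tied to the primary outcome. No listed method includes baseline SARA or the stratum, and the interaction is not mentioned. On size, "the same sample size of 20 SCA3 patients is chosen", ten per arm, with 83% power stated for an effect size of 0.46 at α = 0.05.

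**The concern.** Two features of the stated analysis do not fit the design.

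1. **Stratified but not adjusted.** Stratifying on SARA removes part of the chance imbalance in severity between the arms. An analysis without SARA in the model still counts that severity variation as error. Its standard error is then too large for the design, so the test runs below its nominal level and loses some power. With ten patients per arm there is little power to spare.

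2. **Main effects rather than the interaction.** In a TIME × TREATMENT ANOVA that includes baseline, the TIME main effect is change averaged over both arms. The TREATMENT main effect is the arm difference averaged over time points, including the one before treatment. Neither is the treatment effect on change. That effect is the interaction, which the follow-up rule does not name.

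**Working it through.** **Inputs from the protocol:** 10 per arm; α = 0.05; primary outcome is change from T0 to T1; stratification on pre-study SARA.

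**Assumptions:** two-sided testing; equal SD σ at T0 and T1; normal scores; baseline–T1 correlation r from 0.5 to 0.95 (not in the protocol); for the stratified case, two strata split at the median with 5:5 allocation in each (the protocol gives no cut-points), and the stratifying score taken as the T0 score.

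**The plan's own figure.** The protocol does not say which test or effect-size metric the 83% refers to. For two groups of 10, 0.46 read as d gives 16.4% power. Read as Cohen's f (d = 0.92), it gives 49.5%. About 83% appears for a four-level repeated-measures interaction with λ = f²·N·(m−1) = 0.2116 × 20 × 3 = 12.696 on 3 and 54 df, which gives 83.4%, but the protocol does not state that setting. I therefore use two benchmarks for the change-score test: d = 1.378 (83.0% power) and d = 0.92 (49.5%).

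**Efficiency.** Var(change) = 2σ²(1−r). The ANCOVA residual variance is σ²(1−r²). The ratio is (1−r²)/[2(1−r)] = (1+r)/2. Baseline therefore explains a share (1−r)/2 of the variance of the change score: 25% at r = 0.5 and 2.5% at r = 0.95. Against this, residual df fall from 18 to 17.

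**Simulation** (100,000 runs per setting; power at d = 1.378, change-score t-test → ANCOVA):

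| r | Variance ratio | Type I, stratified: change test | Type I, stratified: ANCOVA | Power, unstratified | Power, stratified |
|---|---|---|---|---|---|
| 0.5 | 0.75 | 3.3% | 4.9% | 83.0 → 90.2% | 84.5 → 91.1% |
| 0.7 | 0.85 | 4.0% | 5.0% | 82.8 → 86.3% | 83.9 → 87.5% |
| 0.8 | 0.90 | 4.3% | 5.0% | 83.2 → 84.5% | 83.6 → 85.6% |
| 0.9 | 0.95 | 4.7% | 5.0% | 82.8 → 82.1% | 83.5 → 84.1% |
| 0.95 | 0.975 | 4.8% | 4.9% | 83.2 → 81.7% | 83.1 → 82.9% |

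The gain is about 7 points at r = 0.5, 3.5 at 0.7 and 1 to 2 at 0.8. At 0.9 and above it lies between +0.6 and −1.5. At d = 0.92 it is larger for moderate r: stratified, 48.8 → 60.0% at 0.5, 49.4 → 55.1% at 0.7 and 49.1 → 52.3% at 0.8. It is still about nil at 0.9 or more (49.6 → 50.5% and 49.7 → 49.6%).

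If T0 SARA correlates only 0.9 with the pre-study score used for stratification, type I error of the change test is 3.7% to 4.9%, and the gains at d = 1.378 are 6.7, 3.7, 1.9, 0.3 and −0.4 points.

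**Which ANOVA term.** With two time levels, the interaction F equals the square of the change-score t, so these are one test with one p-value. The TREATMENT main effect over T0 and T1 estimates half the T1 effect, and its error is the between-patient variance σ²(1+r)/2. A standardised change effect d becomes d·√[(1−r)/(1+r)]: 1.378 × 0.577 = 0.80 at r = 0.5 and 1.378 × 0.229 = 0.32 at r = 0.9. Simulated power of that term under stratification is 35.1%, 14.7%, 7.0%, 2.1% and 0.7% across the five values of r.

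**The case against.** The strongest reply is that a change-score test already uses baseline by subtraction and is valid. That stands. A reader might infer that the plan ignores baseline SARA, leaves imbalance uncorrected or inflates the false-positive rate. The documents do not support this: the outcome is a change, allocation is stratified, and the error rate falls slightly below nominal, not above.

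A reader might also infer that the primary p-value could come from a t-test on T1 scores alone, or from one Bonferroni-corrected contrast among many, with a large loss of power. The protocol assigns neither route to the primary outcome. Table 2 places it at T1 only, and the Discussion puts the focus on T1 versus baseline, so two time levels is the natural reading. The t-test and the interaction then coincide.

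The eligibility section reports that "improvements following cerebellar anodal tDCS were greater in clinically less affected patients". It is tempting to cite this as proof that baseline should be a covariate. It describes a treatment effect that varies with severity, which a common-slope ANCOVA does not model, so it gives the remedy little support.

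Finally, this is a condensed article for a study that calls itself exploratory, and a separate analysis plan may name the model. That limits the weight of the point. It does not remove it: the methods that are stated contain no adjustment, and the stated follow-up rule points at main effects, which a later plan would have to override and not merely elaborate.

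**Conclusion.** The point holds as a matter of efficiency and precise wording, not of validity. After SARA stratification the unadjusted change-score test has a type I error of about 3.3% to 4.8%. ANCOVA holds about 5% and, where the change-score test has about 83% power, gains about 7 points at r = 0.5, falling to nil or a loss of up to about 1.5 points at 0.9 and above. Where power is nearer 50%, the gain at r = 0.5 is 9 to 11 points (49.5 → 58.6% unstratified, 48.8 → 60.0% stratified). These sizes rest on an undocumented correlation and an assumed two-stratum scheme. If SARA is very stable over two weeks, the efficiency argument largely disappears, and what remains is a correct nominal level and a single named test.

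The second part does not depend on r: a main effect in the stated ANOVA does not test the treatment effect on change. The protocol does not say that the primary result will be read from a main effect, so this is a defect in the stated rule and not evidence of a wrong primary test.

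**What to change.** Name one primary analysis: ANCOVA of the T0–T1 SARA change on treatment, with T0 SARA as a continuous covariate and the randomisation stratum added if it carries further information. Test at two-sided α = 0.05, outside the Bonferroni post-hoc family, and report the adjusted mean difference with its 95% CI. Using T1 SARA as the response gives the same treatment estimate.

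If a repeated-measures ANOVA is kept for the secondary time points, base inference on the TIME × TREATMENT interaction and amend the post-hoc sentence accordingly. Tie the power statement to the named test.

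Cost: wording, and one or two degrees of freedom out of 18. No new data or patients are needed. The downside is no power gain, and possibly a loss of about a point, if the baseline–T1 correlation is 0.9 or more.
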